### Statistical Analysis

Continuous, non-normally distributed values will be presented as median and interquartile range (IQR), unless otherwise specified. Discrete variables will be presented as frequency (percentage). Normal distribution of continuous variables will be assessed with the Kolmogorov–Smirnov algorithm. Normally distributed variables among the different groups will be compared using the Student's *t*-test. Non-normally distributed variables will be compared using the Mann–Whitney *U*-test. Categorical variables will be analyzed by the Fisher's exact test or chi-square test.

To compare remission rates, relapse rates, relapse-free survival and long-term outcomes between participants, we will stratify participants according to the date of diagnosis, meeting the different diagnostic criteria, the type of treatment, the glucocorticoids starting dose, the cumulative dose, tapering speed, and treatment with maintenance treatment.

Moreover, to assess the impact of the treatment effect being part of the diagnostic criteria, we will perform sensitivity analyses comparing the study outcomes between those classified as AIP regardless of the steroid trial, and those in whom the diagnosis was dependent on the steroid trial. Sensitivity analyses will also be performed to compare the study outcomes including or excluding individuals that do not meet any available diagnostic criteria, and those classified as NOS-AIP.

Kaplan-Meier curves will be used to assess time-to-relapse. Time-to-relapse will be compared between subgroups using the log-rank test. Univariable and multivariable analyses with a backward selection procedure will be performed to identify possible predictors for relapse, based on a Cox-proportional hazards regression model. A significance threshold of *P* < 0.05 will be used.

Data from national pancreatic cancer registries will be used to determine age- and sex-specific incidence rates for pancreatic ductal adenocarcinoma. Standardized incidence ratios (SIRs) will be then calculated by obtaining the ratio of the observed to the expected number of cases, and 95% confidence intervals (95% CIs).

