## Methods

### Study Design

This is an international, retrospective, observational cohort study including all AIP patients. We used the Pancreas2000 framework (www.pancreas2000.org) to create a study network starting with the six centers in the PrescrAIP core group. Additional European centers with expertise in the treatment of AIP patients have been recruited, accumulating to a total of 44 collaborating centers.

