### Study Endpoints

Our primary endpoints consist of remission of disease (defined as the absence of clinical symptoms and the resolution of pancreatic abnormalities on imaging), relapse of disease, relapse rates compared between patients with a low or a high dose regimen, cumulative maintenance therapy dose and relapse-free survival time. Our secondary study endpoints are gold standard diagnostic tools of AIP compared to U-AIP, the prevalence of pancreatic exocrine insufficiency and the cumulative incidence of pancreatic ductal adenocarcinoma. The diagnosis of diabetes mellitus [as defined by the American Diabetes Association (27)] either before or after steroid treatment is our tertiary study endpoint.

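### Student's t-test after a Kolmogorov–Smirnov check leaves continuous comparisons exposed to unequal spread between unequal regimen groups; Welch's test would remove this at almost no cost

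*Protocol article*

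**What the plan says.** The Statistical Analysis section of the protocol article sets a two-step rule for continuous variables.

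- The check: "Normal distribution of continuous variables will be assessed with the Kolmogorov–Smirnov algorithm".
- If the variable passes: "Normally distributed variables among the different groups will be compared using the Student's" *t*-test.
- If it fails: "Non-normally distributed variables will be compared using the Mann–Whitney" *U*-test, with median and interquartile range as the summary.
- The level: "A significance threshold of *P* < 0.05 will be used". Sidedness is not stated; two-sided is assumed here.

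The article names no unequal-variance form of the *t*-test and no check of spread. It does not say which version of Kolmogorov–Smirnov is meant, or whether it is applied by group or to pooled data.

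The design is observational: "This is an international, retrospective, observational cohort study including all AIP patients". For outcome comparisons, patients are stratified by, among other factors, "the type of treatment, the glucocorticoids starting dose, the cumulative dose, tapering speed, and treatment with maintenance treatment". Categorical variables have their own rule: "Categorical variables will be analyzed by the Fisher's exact test or chi-square test". Time to relapse goes to the log-rank test and predictors of relapse to Cox regression.

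**The concern.** Two separate weaknesses sit in this rule.

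**Unequal spread.** Student's *t*-test in its usual form pools the two group variances. If the groups differ in size and in variance, the pooled standard error is wrong, too small or too large depending on which group has the larger spread. A normality check looks at shape, so a variable can pass it and still have very different SDs in the two groups. No allocation ratio keeps regimen groups balanced here. The Introduction presents steroids as the general treatment and B-cell depletion as a recent option, so marked imbalance is plausible, although no figure is given.

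**The gate.** Kolmogorov–Smirnov in its plain form assumes a known mean and SD. When both are estimated from the same data and no correction is made, it seldom rejects. Moderately skewed variables are then summarised and tested as if normal.

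At stake is the reliability of continuous comparisons between groups: baseline laboratory values, doses, durations, glycaemic measures, and the one plainly continuous item among the primary endpoints in "relapse rates compared between patients with a low or a high dose regimen, cumulative maintenance therapy dose and relapse-free survival time", namely cumulative maintenance dose.

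**Working it through.** The article states no sample size, power, SD or group size, so there is no figure of its own to reproduce. The benchmark is the nominal 5%. All group sizes, SD ratios and skewness values below are assumptions, shown as ranges.

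**1. Student's *t* under equal means.** For large samples,

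type I error ≈ 2 × [1 − Φ(1.96 × √(V_pooled / V_true))]

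where V_pooled = s²_p × (1/n₁ + 1/n₂), s²_p = [(n₁ − 1)σ₁² + (n₂ − 1)σ₂²] / (n₁ + n₂ − 2), and V_true = σ₁²/n₁ + σ₂²/n₂.

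*Smaller group has the larger SD: 30 patients with SD 2, 170 with SD 1.*
- s²_p = (29 × 4 + 169 × 1)/198 = 285/198 = 1.439
- V_pooled = 1.439 × (1/30 + 1/170) = 1.439 × 0.03922 = 0.0564
- V_true = 4/30 + 1/170 = 0.1392
- ratio = 0.405; 1.96 × √0.405 = 1.248; type I error = 21.2% (simulated: 21.0%)

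*The same sizes with SD ratio 1.5.*
- s²_p = (29 × 2.25 + 169)/198 = 1.183; V_pooled = 0.0464; V_true = 2.25/30 + 1/170 = 0.0809
- ratio = 0.574; critical value 1.484; type I error = 13.8% (simulated: 13.4%)

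*Reverse pairing: 170 patients with SD 2, 30 with SD 1.*
- s²_p = (169 × 4 + 29)/198 = 3.561; V_pooled = 0.1396; V_true = 4/170 + 1/30 = 0.0569
- ratio = 2.456; critical value 3.071; type I error = 0.2% (simulated: 0.2%)

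*Equal sizes.* With n₁ = n₂ the pooled and true variances coincide, the ratio is 1, and the error is 5% whatever the SDs.

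Simulated type I error for normal data with equal means (20,000 replicates; Mann–Whitney 4,000):

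| Sizes; the group named first has the larger SD | SD ratio | Student | Welch | Mann–Whitney |
|---|---|---|---|---|
| 100 / 100 | 2 | 5.2% | 5.1% | 6.6% |
| 30 / 170 | 1 | 5.0% | 5.0% | 5.2% |
| 30 / 170 | 1.25 | 9.1% | 5.1% | 7.3% |
| 30 / 170 | 1.5 | 13.4% | 5.2% | 8.5% |
| 30 / 170 | 2 | 21.0% | 5.0% | 11.9% |
| 30 / 170 | 3 | 30.3% | 4.9% | 14.1% |
| 50 / 150 | 1.5 | 10.7% | 5.0% | 8.1% |
| 50 / 450 | 2 | 25.1% | 5.3% | 12.6% |
| 170 / 30 | 1.25 | 2.3% | 5.0% | 3.6% |
| 170 / 30 | 1.5 | 1.0% | 5.2% | 2.8% |
| 170 / 30 | 2 | 0.2% | 5.1% | 1.0% |

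Welch stays at 4.7–5.4% in every scenario run.

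**2. Does the gate rescue the test?** No. The full procedure, Kolmogorov–Smirnov and then the chosen test, for 30 versus 170 at SD ratio 2 with the larger SD in the smaller group, gives 20–21% with the gate applied by group and 16.5–21% with it applied to pooled data.

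**3. What the gate lets through.** Share of skewed samples that pass at 5% (600 replicates):

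| Distribution | n | Plain K–S, estimated mean and SD | Lilliefors-corrected |
|---|---|---|---|
| Gamma, skewness 1 | 30 | 99% | 73% |
| | 100 | 92% | 34% |
| | 200 | 65% | 6% |
| | 500 | 6% | 0% |
| Exponential, skewness 2 | 30 | 86% | 21% |
| | 50 | 65% | 3% |
| | 100 | 7% | 0% |

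**4. Does skew that passes the gate inflate error?** No. With identical skewed distributions in both groups, the overall type I error of the gated procedure is 4.2–5.8%. The cost is in power. For a lognormal variable with log-SD 0.8, 50 per group and a shift of 0.6 log-SD, the raw-scale *t*-test has 72% power against 82% for Mann–Whitney. Those figures take no account of the gate, so the loss arises only in samples that pass it.

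**The case against.** The strongest reply is that this is common textbook wording, and that a condensed article may leave the software option and the Kolmogorov–Smirnov variant to a fuller document. That stands in part. The variant is indeed open, and with the Lilliefors correction the second weakness shrinks. The test itself is named, however, and the named test is by its usual meaning the equal-variance one.

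Three further objections limit the point, and each answers a stronger reading that a reader might be tempted to adopt.

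- *That false-positive rates here are several times 5%.* The documents do not support this. Inflation of that order needs the smaller group to have the larger spread, imbalance of about 3:1 or more, and an SD ratio of roughly 1.5 to 2 or more. At a ratio of 1.25 the error is 8–10%, and the reverse pairing is conservative. No sizes or SDs are given from which to tell which case applies.
- *That skew slipping through the gate causes the inflation.* It does not; step 4 of the working shows error near 5%. Strong skew is also mostly caught in larger groups, and such variables then go to Mann–Whitney under the plan's own rule.
- *That the main effectiveness results are at risk.* They are not. Remission and relapse rates use Fisher's exact or chi-square tests, time to relapse the log-rank test, and predictors of relapse Cox regression.

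It is also fair to object that sending more variables to Mann–Whitney is no cure. Under unequal spread its rejection rate at 30 versus 170 reaches 11.9% at SD ratio 2 and 14.1% at ratio 3.

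**Conclusion.** The point holds as a minor one. The stated rule uses an equal-variance test for groups whose size and spread are not controlled, and relies on a preliminary check that does not address spread. Under the assumed 30 versus 170 split and SD ratios of 1.5 to 2, the actual level is about 13–21% if the smaller group is the more variable and 1% or less if it is the less variable; it is about 5% with equal sizes or equal SDs. The direction and size in the actual data cannot be known from the article. The gate is a separate weakness of description and power, largest for moderate skew in small or moderate groups and for the uncorrected version of the test. The reach is continuous descriptors and cumulative maintenance dose.

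**What to change.** In the Statistical Analysis section:

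- Replace Student's *t*-test with Welch's unequal-variance *t*-test.
- Delete the Kolmogorov–Smirnov gate and fix the summary and test for each variable in advance. Use Welch on the raw scale for roughly symmetric variables such as age, and Welch on the log scale for skewed ones such as serum IgG4, doses and durations, with median and interquartile range as the summary.
- Where Mann–Whitney is kept, present it as a comparison of distributions rather than of means or medians.

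A log-scale comparison concerns ratios of geometric means, and the text should say so. The cost is a few sentences and a software option, with no new data. The loss of power from Welch when variances are in fact equal is negligible. Fixing the method beforehand also removes a data-driven choice of test.

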## Abstract

**Introduction:** Treatment of autoimmune pancreatitis (AIP) is based solely on consensus and has yet to become standardized. Consequently, therapeutic regimens vary greatly between countries and centers, and largely depend on the experience of the physician. At this moment, the optimal regimen for inducing disease remission and preventing relapse is unknown.

**Objectives:** The primary objective of this study is to describe current treatment regimens used in Europe, and to compare their effectiveness in inducing remission and preventing and treating relapse. The secondary objectives are: to identify risk factors for relapse; to assess the diagnostic accuracy of the Unified-AIP criteria; to assess the performance of the M-ANNHEIM score for predicting relapse; and to assess long-term outcomes including pancreatic exocrine insufficiency and pancreatic cancer.

**Methods:** This is an international, retrospective, observational cohort study, performed in over 40 centers from 16 European countries. Eligible are all patients diagnosed with AIP from 2005 onwards, regardless of the used diagnostic criteria. Data on study subjects will be retrieved from the hospital's electronic medical records and registered with a standardized, web-based, electronic case report form (eCRF). To compare the effectiveness of treatment regimens in inducing remission, preventing relapse, and treating relapse, subjects will be stratified in groups based on: type of therapy; initial therapy dose; cumulative therapy dose; therapy tapering speed and duration; and having received maintenance therapy or not.

**Ethics and Dissemination:** Ethical and/or institutional review board approvals are obtained by all participating centers according to local regulations. The study complies with the General Data Protection Regulation (GDPR). All manuscripts resulting from the study will be submitted to peer-reviewed journals.

**Conclusion:** This is the first pan-European retrospective registry for AIP. It will produce the first large-scale data on treatment of European patients with AIP, providing answers on the use and effectiveness of treatment regimens. In the future, this collaboration may provide a network for continuation into a prospective European registry.

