All AIP subtypes respond dramatically to steroid treatment (up to 99% in the different cohorts) (11–14), but the optimal dose to induce remission remains controversial. Reported induction doses have ranges between 30 and 60 mg daily (11–14) Recently, other therapeutic options, that induce B-cell depletion, have also been employed in inducing AIP remission, with promising results (15, 16). In a cohort from France, the reported efficacy was 94% with two infusions given in most patients (17). However, in spite of the dramatic response to initial treatment, the risk of relapse within 1 year from disease remission ranges between 30 and 50% (12), being higher in type 1 than in type 2 AIP patients (12). Several risk factors for AIP relapse have been proposed, but have not been validated prospectively (11, 12, 18, 19). Due to the high frequency of relapse after induction, some authors recommend maintenance treatment with low-dose steroids or immunomodulators, but the patient group that would benefit from maintenance is currently unknown (20–26).

Thus far, data on the epidemiology and natural history of AIP are still scant due to its rarity and its relatively recent appraisal. Most of the data comes from Asian or North-American cohorts, while data on large European cohorts are lacking. As a consequence, treatment options applied in Europe are largely based on retrospective studies from Asian and North-American patients.

We established the PrescrAIP (A Pan-European Study on Current Treatment Regimens of Auto-immune Pancreatitis) study network to retrospectively describe the current status of AIP treatment in Europe on a large scale. In addition, our effort will create the opportunity for a subsequent international prospective registry that will be able to provide definite answers in the future. In particular, in this retrospective multicentre study, we aim to define and compare the AIP treatment regimens used throughout different European centers, highlighting their differential impact on disease remission and long-term outcomes. These results will foster our knowledge of this rare disease, yielding to better patient care.

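### First remission is compared across maintenance, whole-course cumulative dose and taper, which follow remission or are completed after it, so spurious differences in either direction are possible

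*Protocol article*

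**What the plan says.** The Statistical Analysis section of the protocol article names four outcome families and one set of strata: "To compare remission rates, relapse rates, relapse-free survival and long-term outcomes between participants, we will stratify participants according to the date of diagnosis". After diagnostic criteria and type of treatment, the list ends with "the glucocorticoids starting dose, the cumulative dose, tapering speed, and treatment with maintenance treatment". The Abstract does the same: "To compare the effectiveness of treatment regimens in inducing remission, preventing relapse, and treating relapse, subjects will be stratified in groups based on" a list that includes "cumulative therapy dose; therapy tapering speed and duration; and having received maintenance therapy or not".

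Under Study Endpoints, remission is a primary endpoint, defined as "the absence of clinical symptoms and the resolution of pancreatic abnormalities on imaging". The article gives no time at which it is assessed. For categorical data the stated tests are simple ones: "Categorical variables will be analyzed by the Fisher's exact test or chi-square test", with a threshold of P < 0.05.

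On the place of maintenance, the Introduction says: "Due to the high frequency of relapse after induction, some authors recommend maintenance treatment with low-dose steroids or immunomodulators". In the article's own account, maintenance comes after induction and its purpose is to prevent relapse.

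**The concern.** A comparison of regimens for inducing remission needs exposures that precede the outcome. Starting dose and first therapy do. Maintenance, as the article describes it, does not. Whole-course cumulative dose and taper speed or duration lie in between: they begin before remission is assessed, but their final values depend on what happens afterwards. In a retrospective cohort where treatment is not assigned, the course may be shortened, prolonged or extended into maintenance according to how the patient responded. The outcome then helps to decide the exposure group.

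Inducing remission is the first effectiveness question in the primary objective. A spurious association there could be read as evidence about which regimen induces remission.

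**Working it through.** **Plan's own figure.** The article gives no sample size, event count or power, so there is nothing to reproduce. The check asks what the planned contrast shows when remission is unrelated to every regimen feature.

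**Inputs.** The tests and the 0.05 threshold come from Statistical Analysis (taken as two-sided). The Introduction cites steroid response of up to 99%, and 94% efficacy of B-cell depletion in one cohort. Neither is necessarily remission as defined under Study Endpoints. Cohort size, remission rate and the dependence of treatment on response are assumptions.

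**1. Maintenance, by arithmetic.** Let p be the remission rate, m1 the share of remitters given maintenance and m0 the share of non-remitters given it.

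- Remission with maintenance = p·m1 / [p·m1 + (1−p)·m0]
- Remission without = p(1−m1) / [p(1−m1) + (1−p)(1−m0)]

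With p = 0.90, m1 = 0.40, m0 = 0.10:

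- with: 0.36 / (0.36 + 0.01) = 97.3%
- without: 0.54 / (0.54 + 0.09) = 85.7%

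Varying m0, with Fisher's test in simulated cohorts of 400:

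| m0 | With maintenance | Without | P < 0.05 |
|---|---|---|---|
| 0% | 100% | 84.4% | 100% |
| 10% | 97.3% | 85.7% | 98% |
| 20% | 94.7% | 87.1% | 70% |

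**2. The sign is not fixed.** With p = 0.85, suppose clinicians instead keep non-remitters on treatment, so that m1 = 0.25 and m0 = 0.50:

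- with: 0.2125 / (0.2125 + 0.075) = 73.9%
- without: 0.6375 / (0.6375 + 0.075) = 89.5%

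Maintenance now looks harmful. If m1 = m0, both rates equal p and the difference vanishes.

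**3. Cumulative dose.** Assumptions: 400 patients, 90% remission, log-normal dose (log-SD 0.4), split at the median, non-remitters' dose multiplied by a factor.

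| Factor | Upper half | Lower half | P < 0.05 |
|---|---|---|---|
| 1.10 | 88.3% | 91.7% | 17% |
| 1.25 | 86.2% | 93.8% | 69% |
| 1.50 | 83.5% | 96.4% | 99% |

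With no dependence on response, the rejection rate was about 4%.

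**4. All strata together.** A second simulation used 600 patients, 85% remission and the chi-square test.

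| Stratum | Non-remitters treated longer | Maintenance mainly to remitters (30% v 5%) |
|---|---|---|
| High v low cumulative dose | 77.3% v 91.9%, rejected 100% | 88.8% v 81.4%, rejected 72.0% |
| Slow v faster taper | 79.1% v 88.3%, rejected 84.7% | no difference, rejected 5.1% |
| Maintenance v none | 74.0% v 89.5%, rejected 99.4% | 97.1% v 80.6%, rejected 100% |
| Starting dose | 85.0% v 85.0%, rejected 5.6% | no difference, rejected 4.8% |

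In the first pattern, half of the non-remitters had a slower, longer course, and maintenance went to 50% of non-remitters and 25% of remitters. Over all scenarios, starting dose was rejected in 3.1% to 6.2% of cohorts. The three later strata stayed at 4.0% to 5.7% when later treatment ignored response.

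**5. Dependence on the remission rate.** In the model of steps 1 and 3 at 95% remission, rejection for maintenance with m0 = 10% or 20% is about 80% or 38%. For a dose factor of 1.10 or 1.25 it is about 9% or 38%. At 99% every setting gives 1% to 13%. In the 600-patient model at 99%, with non-remitters treated longer, it is 25.7% for dose, 14.8% for taper and 31.3% for maintenance.

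**The case against.** The strongest reply has five parts.

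- **Timing.** A reader might infer that all three variables are settled only after remission is reached or missed. That fits maintenance alone. Dose accrues from the first day, and a taper can start before the imaging that defines remission. The Discussion raises tapering speed alongside starting dose in its sentence on induction, so dropping taper from the remission question would discard something the study wants to know. This stands, and it is why dose and taper should be re-measured rather than removed.
- **Mechanism.** No section says that non-responders are kept on drug or escalated, or that only remitters receive maintenance. A reader might infer that the maintenance group is in remission by construction, but the article does not say so. This also stands: the bias is conditional on response-adapted treatment.
- **Direction.** A reader might infer that the plan will show maintenance and lower cumulative dose as better for induction. Steps 2 and 4 show that either sign can arise.
- **Condensed wording.** Study Endpoints attaches the low-versus-high dose contrast to relapse, and the variable definitions are in an appendix that is not shown, so cumulative dose might mean induction dose. For treating relapse, earlier maintenance does precede the second remission, and that pairing is sound. Even so, two sections state one list for all outcomes and name remission in it. No section limits these strata to relapse or sets a landmark.
- **Descriptive study.** The article calls itself descriptive and leaves definite answers to prospective work. But its primary objective is to compare effectiveness in inducing remission. Describing the regimens is unaffected; testing remission across these strata is what is in doubt.

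The sensitivity analyses do not help, because they address diagnostic certainty and the steroid trial. The Cox model is for relapse only.

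**Conclusion.** The concern holds in conditional form. Maintenance as the article describes it cannot have induced first remission, so that contrast has no meaning for induction whatever its size. Whole-course cumulative dose and taper can be shaped by response, and the contrasts by them are then biased.

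The size rests on assumptions about how treatment followed response. With 90% remission and 400 patients, a gap of 97.3% v 85.7% arises with no treatment effect if 40% of remitters and 10% of non-remitters receive maintenance. Rejection rates run from about the nominal level to 100% across the settings examined, and fall markedly as remission approaches 99%. The article supports neither a fixed direction nor the claim that false differences are certain. Starting dose is not affected by this mechanism. Confounding by indication is a separate matter that remains for every stratum.

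**What to change.** Split the list of strata by outcome in the Abstract and in Statistical Analysis.

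- **First remission:** compare by features fixed at treatment start, namely type of first therapy, starting dose, date of diagnosis and diagnostic criteria met.
- **Cumulative dose and taper, for first remission:** use only values measured within a fixed early window stated in advance, among patients not yet classified as in remission when it ends, and count remission assessed afterwards.
- **Maintenance:** use only for outcomes after first remission, including relapse and the treatment of relapse.

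This is a change of wording. The windowed analysis needs dated dose and remission records; the article says that type, dose and duration of treatment are collected. The cost is that the crude whole-course dose, taper and maintenance contrasts for first remission are dropped or replaced. Patients who remit within the window do not contribute to the windowed contrast, so it answers a narrower question in fewer patients.

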## Objectives

The primary objective of this study is to describe AIP treatment regimens across Europe, and to compare the effectiveness of treatment regimens in inducing remission, preventing and treating relapse. The secondary objectives include identifying risk factors for relapse, assessing the diagnostic accuracy of the U-AIP criteria (6), assessing the performance of the M-ANNHEIM score for predicting relapse (19), and assessing long-term outcomes including pancreatic exocrine insufficiency and pancreatic cancer. Thirdly, we are aiming to assess whether standard treatment was altered due to pre-existing diabetes mellitus, determine the prevalence of diabetes mellitus before and after steroid treatment, assess glycemic control in patients with diabetes mellitus and to describe the clinical, radiological and pathological characteristics of a cohort of patients diagnosed with AIP through pancreatic resection.

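### Relapse-free time is compared between groups defined by treatment received after follow-up starts (cumulative dose, tapering, maintenance), which can produce an apparent effect where none exists unless these are settled at time zero

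*Protocol article*

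**What the plan says.** The Objectives section makes it part of the primary objective "to compare the effectiveness of treatment regimens in inducing remission, preventing and treating relapse". The Statistical Analysis section sets out how: "To compare remission rates, relapse rates, relapse-free survival and long-term outcomes between participants, we will stratify participants according to" a list that ends with "the glucocorticoids starting dose, the cumulative dose, tapering speed, and treatment with maintenance treatment". The Abstract gives the same grouping in slightly different words, by "cumulative therapy dose; therapy tapering speed and duration; and having received maintenance therapy or not".

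For the time-to-event outcome, Kaplan-Meier curves are planned and "Time-to-relapse will be compared between subgroups using the log-rank test". A Cox model is also planned: "Univariable and multivariable analyses with a backward selection procedure will be performed to identify possible predictors for relapse". Its candidate covariates are not listed.

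The Study Endpoints section includes "cumulative maintenance therapy dose and relapse-free survival time" among the primary endpoints.

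The article does not state when the relapse clock starts, over what period dose is accumulated, or whether dose given to treat a relapse counts. The planned sensitivity analyses all concern certainty of diagnosis: dependence on the steroid trial, NOS-AIP, unmet criteria, and raised IgG4 without biopsy or other organ involvement. The limitations in the Discussion cover changing use of guidelines and subtype misclassification. Timing of exposure is not mentioned.

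**The concern.** A log-rank comparison is valid when group membership is fixed at the time from which survival is counted. Type of first therapy and starting dose meet that condition. Three of the listed groupings need not:

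- **Maintenance yes/no.** If maintenance starts some time after the clock does, a patient must stay relapse-free until then to be counted as maintained. Anyone who relapses sooner is counted as not maintained. The maintained group is credited with event-free time that its treatment did not produce (immortal time).
- **Cumulative dose and duration.** If accrual stops at relapse, longer relapse-free time produces a longer course and a higher dose. If re-treatment of relapse is counted, relapse itself raises the dose (reverse causation).
- **Tapering speed.** It is known only once the taper has advanced, and it may have been changed in response to symptoms.

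These are main comparisons of the study. The Introduction presents the question of who benefits from maintenance as open, and the Discussion says the same of tapering speed. Adjusting for baseline covariates does not remove a bias built into the group definition, and a larger cohort makes a false result more likely to reach significance.

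**Working it through.** The article gives no sample size, event count or effect size, so there is no planned figure to reproduce. The check asks what the stated comparison returns when treatment has no effect.

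**Inputs from the document.** One-year relapse risk after remission of 30% to 50% (Introduction); significance threshold 0.05 (Statistical Analysis; two-sided assumed).

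**Assumptions, none given in the document.** Relapse-free patients start maintenance 0, 1.5, 3 or 6 months after time zero (remission). In the main run, 30% are intended for maintenance, N is 200 or 400, follow-up is uniform over 1–5 years, relapse times are exponential, courses last 3–12 months and stop at relapse, and dose is split at the median. There were 1,000 simulated data sets per scenario.

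**Step 1: share misallocated.** With constant hazard, the share relapsing before maintenance would start at time s (in years) is 1 − (1 − p)^s, where p is the one-year risk. For p = 0.30 and s = 0.25 this is 1 − 0.70^0.25 = 8.5%. For p = 0.50 and s = 0.5 it is 1 − 0.50^0.5 = 29.3%. All of these relapses are counted in the no-maintenance group.

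**Step 2: ever versus never maintenance, true HR 1.00.** Each pair shows N = 200 / N = 400.

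| Start | 1-year risk | Relapsed before start | HR as planned | False positives (nominal 5%) | Landmark HR |
|---|---|---|---|---|---|
| 0 | 30% | 0% | 1.00 / 1.00 | 4.8% / 4.4% | 1.00 / 1.00 |
| 0 | 50% | 0% | 1.01 / 1.00 | 4.0% / 4.9% | 1.01 / 1.00 |
| 1.5 months | 30% | 4.4% | 0.90 / 0.91 | 7.6% / 9.4% | 0.99 / 1.00 |
| 1.5 months | 50% | 8.3% | 0.87 / 0.88 | 11.0% / 17.5% | 1.00 / 1.01 |
| 3 months | 30% | 8.5% | 0.82 / 0.83 | 14.3% / 24.3% | 1.00 / 1.00 |
| 3 months | 50% | 15.9% | 0.76 / 0.77 | 33.1% / 55.6% | 0.99 / 1.00 |
| 6 months | 30% | 16.3% | 0.68 / 0.68 | 40.7% / 74.3% | 0.99 / 0.99 |
| 6 months | 50% | 29.3% | 0.61 / 0.61 | 74.7% / 97.4% | 1.01 / 1.01 |

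The landmark is placed at the start of maintenance; its false-positive rate is 3.3–6.9%.

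**Step 3: other assumptions.** Letting the relapse hazard fall over time (Weibull shape 0.6), with uptake of half and follow-up of 2–8 years, strengthens the effect because more relapses come early. Over all settings tried, the HR is about 0.7–0.9 for a start at 1.5 months and about 0.8–0.45 for starts at 3–6 months.

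**Step 4: high versus low cumulative dose, true HR 1.00.** Dose accrued until relapse or end of course gives HR 0.47–0.57 in the main run, with 87–100% false positives, and 0.34–0.59 under other assumed settings. Adding a re-treatment course at relapse gives 1.27–2.35 in the main run but 0.83–3.07 under other settings, so the direction is not fixed. Classifying by dose accrued up to a 6-month landmark gives 0.90–1.03.

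**Step 5: tapering speed.** This was not simulated. The mechanism applies, but neither size nor direction is established.

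**The case against.** The strongest reply is that the article condenses a fuller protocol, and that definitions are placed in an appendix not shown here. The bias turns on such details. If maintenance is always decided at time zero, the check itself finds none. If the clock starts only after the taper is complete, it also disappears for tapering. This part stands: the harm is conditional, and its size rests on assumed timings.

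It does not dispose of the point. The article does fix the comparison: groups by treatment received, compared with a log-rank test. Nothing in it says that cumulative dose, tapering and maintenance are settled at the start.

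A reader might infer more than the text supports:

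- *That the plan is bound to report a false effect.* It is not, because the time origin is open.
- *That the bias is nearly total.* A median split of cumulative maintenance dose gives HR 0.03–0.07 in a null simulation. However, the plan names cumulative therapy dose as the grouping and lists cumulative maintenance dose only as an endpoint, so that figure tests an analysis not clearly stated.
- *That the Cox model enters these exposures as fixed covariates.* No covariates are listed, and the model serves the secondary aim of finding predictors.
- *That listing cumulative maintenance dose as an endpoint is a serious error.* The primary objective is partly descriptive, and the quantity is legitimate for that. The point is minor.

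The article also calls the study descriptive and leaves definite answers to prospective work. That tempers the claims, but it does not remove the stated comparative objective or the significance test.

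**Conclusion.** The concern holds in conditional form. The stated comparison of relapse outcomes by maintenance, cumulative dose and tapering is valid only if these are settled when the clock starts, which the article does not say, and no planned sensitivity analysis would reveal the problem. The mechanism follows from how the groups are defined. Without re-treatment in the dose, the direction is a spurious benefit for maintenance and for higher dose or longer courses. With re-treatment counted, that bias may be offset or reversed.

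The sizes in the working apply only under the assumed start times, course lengths, uptake, follow-up and relapse-time shape; the relapse risk is the only epidemiological input taken from the document. The consequence is still serious for a primary question: under a 3-month start, the false-positive rate already runs from 14% to 56%.

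**What to change.** 1. State the time origin for relapse-free survival, the period over which dose is accumulated, and whether re-treatment of relapse counts.
2. For maintenance, cumulative dose and tapering, replace the fixed-group log-rank comparison with a landmark analysis. Set the landmark before outcomes are examined, classify exposure only from therapy received up to it, include only patients relapse-free at the landmark, and count relapse from there.
3. As a check, fit a Cox model with maintenance and cumulative dose as time-dependent covariates, with exposure cut off at first relapse.
4. Keep fixed-group comparisons for type of first therapy and starting dose.
5. Use cumulative maintenance dose as a descriptive quantity or an exposure, not as an endpoint of effectiveness.

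The cost is wording and some programming. The Assessment Variables section says that type, dose and duration of treatment are recorded; whether start and stop dates are detailed enough for step 3 should be confirmed. Patients who relapse before the landmark leave that analysis, and some precision is lost. In null simulations the landmark removed the bias for maintenance and largely removed it for dose; it was not tested for tapering, and the time-dependent model was not simulated. Neither method removes confounding by indication, including dosing that responds to symptoms, and the report should say so.
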